**Methods/Design:**

346 patients suffering from an umbilical or epigastric hernia will be included in a multi-centre patient-blinded trial, comparing mesh repair with patch repair. Randomisation will take place for the two operation techniques. The two devices investigated are a flat pre-peritoneal mesh and a Proceed Ventral Patch®. Stratification will occur per centre. Post-operative evaluation will take place after 1, 3, 12 and 24 months. The number of complications requiring treatment is the primary endpoint. Secondary endpoints are Verbal Descriptor Scale (VDS) pain score and VDS cosmetic score, operation duration, recurrence and costs. An intention to treat analysis will be performed.

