### Calculation of random sample size

The primary outcome is the number of complications that require treatment. These are defined in detail further in the protocol. The occurrence of complications up to 23% is described [4]. Trials involving patch repair report a much lower complication rate, but the number of trials is significantly less. It is assumed that a conventional procedure leads to a complication in 20% of the cases [4,20]. The hypothesis is that this is reduced to 10% if a patch is used for repair. At a significance level of 5% and a power of 90%, the random sample size is 137 patients per group in a bilateral t-test. In the result analysis a Mann–Whitney parametric test will be used to evaluate a normal distribution. Therefore, the sample size must be increased by 15% [21]. Taking a minimum of 10% loss-to-follow-up into account as well, the total number of patients to be randomized becomes 346.

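### Randomising 346 patients covers a loss of about 8.7 to 8.9% on the protocol's own sample-size chain, not the 10% it states

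*Protocol article*

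**What the plan says.** All the steps are in the protocol article, under Calculation of random sample size:

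- Assumed complication rates: "It is assumed that a conventional procedure leads to a complication in 20% of the cases", and for the patch, "The hypothesis is that this is reduced to 10% if a patch is used for repair".
- Base figure: "At a significance level of 5% and a power of 90" per cent, "the random sample size is 137 patients per group in a bilateral t-test".
- Uplift for the planned Mann–Whitney test: "Therefore, the sample size must be increased by 15" per cent.
- Loss allowance and total: "Taking a minimum of 10% loss-to-follow-up into account as well, the total number of patients to be randomized becomes 346".

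The abstract (Methods/Design) repeats the total without a loss rate: "346 patients suffering from an umbilical or epigastric hernia will be included". No other section gives a different loss rate or a different total. The article does not say whether the 10% was multiplied on or divided out, or where rounding took place.

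**The concern.** An allowance for loss to follow-up is meant to leave the required number of evaluable patients after the stated loss. To survive a 10% loss, the required number has to be divided by 0.90. Adding 10% and then losing 10% leaves 1.10 × 0.90 = 99% of what was needed. The total of 346 looks like the result of adding rather than dividing.

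The allowance bears on the primary endpoint. Complications are counted up to three months, and the three-month contact is a questionnaire that the patient returns (Follow-up and flow chart protocol; Questionnaire P2). The loss is also described as a minimum, so the total falls short at the lowest loss the plan expects. If the step is reused when the base figure is revised, the same 1% shortfall carries into the new total.

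**Working it through.** **Inputs, all from Calculation of random sample size:** base 137 per group, two groups (equal allocation is read from the wording per group), uplift 15%, loss 10%, total randomised 346.

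**1. Number the chain requires**
- Per group: 137 × 1.15 = 157.55, or 158 in whole patients.
- In total: 2 × 157.55 = 315.1, or 2 × 158 = 316.

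**2. Reproducing 346**
- On the total: 315.1 × 1.10 = 346.61, which gives 346 if the fraction is dropped.
- Per group: 157.55 × 1.10 = 173.3, which ordinary rounding makes 173, and 2 × 173 = 346.
- Per group from 157: 157 × 1.10 = 172.7, which rounds to 173, again giving 346.

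So multiplying by 1.10 reaches 346 by more than one rounding route.

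**3. Dividing out the loss**
- On the total: 315.1 / 0.90 = 350.1, so 351.
- In equal whole arms: 158 / 0.90 = 175.6, so 176 per arm and 352 in total.
- Even starting from 157 per arm: 157 / 0.90 = 174.4 per arm, about 349 in total.

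No rounding of the division route gives 346.

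**4. What 346 delivers (this step needs no assumption about the method used)**
- Left after a 10% loss: 346 × 0.90 = 311.4, or 155.7 per arm.
- Shortfall: 315.1 − 311.4 = 3.7, about 4 patients. Against 316 it is 4.6, about 5.
- Loss covered: 1 − 315.1/346 = 8.9%, or 1 − 316/346 = 8.7%.

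**5. Size of the effect**
- Extra patients under division: 351 − 346 = 5 (5/346 = 1.4%) or 352 − 346 = 6 (6/346 = 1.7%).
- Power on the plan's own scale, taking 157.55 per arm as giving 90% at two-sided 5%: the standardised effect is 1.960 + 1.282 = 3.242. At 155.7 per arm it becomes 3.242 × √(155.7/157.55) = 3.222. Power is Φ(3.222 − 1.960) = Φ(1.262) = 89.7%, a loss of about 0.3 points.

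**6. The base figure, checked separately**

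For 20% versus 10% compared as two proportions, two-sided 5% and 90% power:

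n = [1.960 × √(2 × 0.15 × 0.85) + 1.282 × √(0.20 × 0.80 + 0.10 × 0.90)]² / 0.10² ≈ 266 per group.

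With 137 per group, power is about 64%. With 176 per group evaluable (352 in all, with no loss) it is about 75%.

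**The case against.** **The method is inferred.** The article says only that the loss was taken into account. A reader might conclude from 346.61 that the authors truncated the total and so dropped a patient. The document does not support that: it shows no rounding step, and ordinary rounding per arm also gives 346. This objection stands against any claim about how the figure was reached. It does not touch step 4, since 346 less 10% is below 315.1 whatever the route.

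**The property is not spelled out.** The article never says in so many words that 315 patients will remain. That is true, but an allowance for loss in a sample-size calculation has no other natural meaning.

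**The shortfall is immaterial.** Five or six patients and 0.3 points of power decide nothing in this trial. This stands, and it limits the weight of the point.

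**The target is not worth defending to within four patients.** The base of 137 is far too small. The 15% uplift is also doubtful for a yes/no outcome, because the Post-operative analysis section assigns the chi-square or Fisher test to categorical data. Without the uplift the chain needs 274, and 346 would cover a loss of 1 − 274/346 = 21%. The objection is fair, and it means the 8.7 to 8.9% holds only on the chain as published. It does not rescue 346, since the base remains too small.

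**A larger loss.** A reader might also suppose that more than 10% will be lost. The documents give no reason to expect this: the primary window is three months, and telephone contact with non-responders is planned. The point does not rely on it.

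**Conclusion.** The point holds as a small arithmetic correction. On the published chain, the stated total does not absorb the stated minimum loss. This rests on the chain being kept as written (137 per group, 15% uplift, equal groups) and on the allowance meaning that the required number should remain after the loss. That 346 came from multiplying by 1.10 is a likely explanation, not a documented fact.

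A reader might infer that moving from 346 to 352 would put the trial's power right. It would not. The stated 90% power fails mainly because of the base figure, and correcting the loss step alone leaves that failure almost unchanged.

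**What to change.** In Calculation of random sample size, replace the claim of a minimum 10% loss with a statement that, on the present chain, 346 randomised patients cover a loss of about 8.7 to 8.9%. The 10% wording has to go at the same time, or the sentence will contradict itself. The abstract gives no loss rate and needs no change. The cost is one sentence and no extra patients.

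When the base of 137 is corrected, compute the new total as number needed / (1 − loss), rounded up within each group, and state that formula. If 352 is mentioned, say that it corrects only the loss step.

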### Participant recruitment and retention

The surgeon will recruit the patients. Participation is not stimulated in any way other than voluntary participation.

### Randomisation

Sequence generation and randomisation will be performed by http://www.random.org/. The generated sequence is printed on paper cards with randomization numbers. These cards are put in non-see through envelopes. These envelopes can only be opened in the operating theatre just before timeout procedure, without informing the patient about the outcome of randomisation

### Blinding

The trial is a patient-blinded type. The patient is informed on the type of mesh device used by means of the questionnaire after 24 months (P3). In the data handling phase of the, the annalist is blinded for treatment. The consulted physician during follow-up is not blind for the received treatment.

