### Follow-up and flow chart protocol

The surgeon must fill in a questionnaire (D1) immediately after the operation. The patients are advised to take 1 gram of paracetamol 3 times a day for the first 2 weeks, and to begin mobilizing immediately according to their capacity. Follow-up at the outpatient clinic takes place after 1 and 12 months, with the practitioner filling in the questionnaires (D2 and D3). The patients are asked to fill in a questionnaire 3 and 24 months after the operation (P2 and P3). These questionnaires will be sent to the patients by postal service or e-mail. Non-responders were contacted up to three times by means of a telephone questionnaire. Figure 1 shows the studies flow-chart.

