#### Questionnaire P3 – by the patient – 2 years postoperative

Collected data: recurrence, use of analgesics at that time, VDS pain score at rest, pain score while exercising and VDS cosmetic score.

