### Publication

The plan is to create three publications. The primary endpoint with short-term results will be processed in one report. This will be one month post-operatively. The the long-term results will be processed in two another report. One report with one-year results and one with two-year result. In the two-year results report, recurrence will be added as secondary outcome measure. Co-investigators with a contribution of at least 10% of the number of patients required will be asked for co-authorship.

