## Discussion

This trial is one of the first in its kind, to compare different sorts of mesh types in a randomized controlled setting. Lots of mesh devices are available for herniorraphy made by various companies. Often the choice of the mesh depends on the personal favour of the operating surgeon. The reason to start with this trial is to have a more scientific approach for the decision-making regarding the determination of mesh device.

In this study protocol only the patient is blinded for the treatment. By all means, the operating surgeon cannot be blinded for the type of mesh. The doctor who sees the patients in the outpatient clinic, and fills in forms D2 an D3 can be blind for the treatment type. Because of logistical reasons this is not added to this study protocol. Besides the logistical reasons we think that there is little value in blinding the treating doctor in the outpatient clinic. Observer-bias will be very little because of the straightforward multiple-choice questions in forms D2 and D3.

The results will help to evaluate mesh repair for epigastric an umbilical hernia, and find a surgical device/method that minimizes the complication rate. Besides complication rate, recurrence and costs are taken in account.

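### Allocation is disclosed to the patient through P3, the same form that collects the 24-month patient-reported outcomes, and nothing delays disclosure until the answers are in

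*Protocol article*

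**What the plan says.** The Blinding section states "The trial is a patient-blinded type" and then sets out how the blind ends: "The patient is informed on the type of mesh device used by means of the questionnaire after 24 months (P3". The same section says of the clinicians: "The consulted physician during follow-up is not blind for the received treatment". The data analyst is blinded, but the Discussion confirms that on the treatment side "In this study protocol only the patient is blinded for the treatment".

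P3 is defined under the heading "Questionnaire P3 – by the patient – 2 years postoperative". Its content is: "Collected data: recurrence, use of analgesics at that time, VDS pain score at rest, pain score while exercising and VDS cosmetic score".

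On delivery, the Follow-up section says of the 3- and 24-month forms: "These questionnaires will be sent to the patients by postal service or e-mail". Data collection methods adds that P3 comes from the coordinating hospital. Non-responders are telephoned up to three times. Outpatient visits are at 1 and 12 months only.

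On use of the data, Objectives/Endpoints follows pain to 24 months, the Post-operative analysis section lists pain, analgesics, cosmetic score and recurrence with 24 months among the time points, and the Publication section says: "In the two-year results report, recurrence will be added as secondary outcome measure".

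**The concern.** P3 has two functions that conflict. It tells the patient which device was implanted, and it asks the same patient to rate the result. Pain and appearance are subjective ratings. Recurrence at 24 months is the patient's own report, with no examination described at that time. A patient who knows whether a patch or a conventional mesh was used may answer differently.

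The patient's blind carries particular weight in this trial because the follow-up physician has none. Once the patient is told, neither the person giving the answers nor the treating doctor is blind. The blinded analyst does not help, because any bias is already in the recorded score and cannot be removed in analysis. At stake is whether the two-year report can describe its patient-reported results as patient-blinded.

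**Working it through.** The point concerns the timing and route of disclosure. It depends on no sample size, rate or power figure, and the plan has no figure to reproduce, so the check is a cross-reading of sections.

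1. **When and how the blind ends (Blinding).** At 24 months, by means of P3.
2. **What P3 collects (P3 section).** Two pain scores, analgesic use, cosmetic score and recurrence, all completed by the patient. The form that discloses is the form that measures.
3. **Whether another 24-month source exists (Follow-up; D1 to D3; P1 to P3).** Doctors complete forms at operation, 1 month (D2) and 12 months (D3). Patients complete forms before operation, at 3 months (P2) and at 24 months (P3). P3, or its telephone substitute, is the only described source of these outcomes at 24 months.
4. **Whether completion is controlled (Follow-up; Data collection methods).** The form is posted or e-mailed and no supervision is described, so a recipient can read all of it before answering any of it.
5. **Whether a safeguard is stated.** No section makes disclosure conditional on return of the answers.
6. **Non-responders (Follow-up).** A patient telephoned for not responding has already been sent P3. A disclosure anywhere in that mailing can precede the answers given by telephone.
7. **What precedes disclosure.**

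| Assessment | Time | Relative to disclosure |
|---|---|---|
| Primary endpoint, complications | to 3 months | before |
| D2: pain, analgesics, cosmetic score | 1 month | before |
| P2: pain, analgesics, cosmetic score, recurrence | 3 months | before |
| D3: pain, analgesics, cosmetic score, recurrence | 12 months | before |
| P3: pain, analgesics, cosmetic score, recurrence | 24 months | same form |

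Only the last row is exposed.

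**Can the bias be sized?** A trial calculation shows that the answer depends almost wholly on what is assumed. Take 346 × 0.90 / 2 ≈ 156 patients per arm, no true difference, and reporting that moves the arms apart by d to rates p1 and p2. The standard error is √{[p1(1−p1) + p2(1−p2)]/156}, z = d/SE, and the chance of a two-sided 5% test rejecting is Φ(z − 1.96) + Φ(−z − 1.96).

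| Assumed true rate | Reported rates | SE | z | Chance of rejection |
|---|---|---|---|---|
| 20% | 22.5% v 17.5% | 0.0452 | 1.11 | about 20% |
| 10% | 11.25% v 8.75% | 0.0339 | 0.74 | about 11% |
| 5% | 5.625% v 4.375% | 0.0247 | 0.51 | about 8% |
| 5% | 7.5% v 2.5% | 0.0245 | 2.04 | about 53% |

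The first three rows use the same relative shift (±12.5%); the last uses a 5-point gap, as large as the event rate itself. The 20% is the plan's assumed complication rate, an endpoint that this disclosure cannot reach. The 5% and 10% lie within the 1 to 10% recurrence after mesh that the Background gives for large hernias. No shift has any basis in the document. The pain score is ordinal with four categories, so a comparison of two proportions does not represent it without dichotomising. None of these figures should be read as an estimate.

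**The case against.** The strongest reply is that the order of events is inferred. The article says that the patient is informed by means of P3; it does not say that the device is named before the questions. The disclosure might stand on the last page, and the layout of a form is a detail that a condensed article may leave out. This stands in part: the text does not show that patients know their device when they answer. It does not remove the point, because a mailed form can be read through first and patients reached by telephone have already been sent it. The article positively states the route of disclosure, so this is more than an omitted detail.

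It can also be said that the blind was only ever meant to last to 24 months. That is so, but the plan still collects and reports outcomes at 24 months, and the Discussion's argument that observer bias will be small covers only D2 and D3, the doctors' forms.

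Three stronger readings are tempting and not supported:

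- **That every 24-month outcome is unblinded self-report.** Costs to two years are computed from visits, operation duration, prosthesis costs and complication costs, not from the patient's ratings.
- **That recurrence rests on 24 months alone.** It is also collected at 3 months from patients still blinded and at 12 months by a doctor in clinic, and the Post-operative section lists these time points for analysis. The 12-month doctor is unblinded, but that is a separate matter.
- **That the false-positive rate rises to some stated value, such as 20%.** That figure follows from an assumed reporting shift and a borrowed complication rate.

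**Conclusion.** The point holds with a limited scope. Following the plan as written leaves patient blinding unprotected for pain at rest, pain on exercise, analgesic use, cosmetic score and patient-reported recurrence at 24 months, in up to 346 patients. The primary endpoint and all assessments to 12 months are untouched by this disclosure. The conclusion rests on two readings of the text: that P3 is the vehicle of disclosure, which is stated, and that nothing holds disclosure back until the answers are in, which follows from the absence of any such condition. It does not rest on where the device is named on the form. Neither the direction nor the size of any bias can be derived from the document. The matter is worth correcting because these data feed the two-year report and the remedy is cheap; it does not threaten the trial's main comparison.

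**What to change.** Remove the disclosure from P3. Tell each patient the device in a separate letter or e-mail, sent only after the completed P3 has been received or, for non-responders, after the last telephone attempt. Amend the Blinding section to say that patients stay blinded until that point.

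The cost is one later letter or e-mail per patient, at most 346, and a change of wording. Sample size, analysis and clinical care do not change.

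If P3 forms carrying the disclosure have already been sent, keep a record of which ones, and report the 24-month patient-reported outcomes from those forms as potentially unblinded.

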### Data outcome

A Verbal Descriptor Scale (VDS) is a scale of consecutive descriptions. The following terms are used in the VDS pain score, from which patients can choose to express the level of pain: None, Mild, Moderate, Severe.

#### Questionnaire P1 – by the patient – preoperative

Collected data: height, weight, VDS pain score at rest, pain score while exercising and VDS cosmetic score, comorbidity and daily workload.

#### Questionnaire D1 – by the doctor – peroperative

Collected data: randomised device used (mesh/patch), presence of incarceration, resection of the hernia protrusion, number of fingers for the width of the herniation orifice, the need of widening the herniation orifice, closure of fascia over mesh, presence of adhesions when placing the device intraperitoneally, operation duration, VDS ease, possible reasons protocol violation.

#### Questionnaire D2 – by the doctor – 1 month postoperative

Data collected are: complications, use of analgesics at that time, VDS pain score at rest, pain score while exercising and VDS cosmetic score.

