## Methods

### Design

The MORPHEUS trial is a multicentre, randomized controlled, nationwide, patient-blinded, superiority study. Patients will be randomly allocated to undergo open flat mesh repair or open patch repair for primary umbilical or epigastric hernias. The aim of this study is to determine the ideal treatment for patients with these conditions in terms of operation related complication and postoperative pain.

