#### Questionnaire D3 – by the doctor – 1 year postoperative

Collected data: recurrence, use of analgesics at that time, VDS pain score at rest, pain score while exercising and VDS cosmetic score.

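### At 1 and 12 months the VDS pain and cosmetic scores are recorded by a practitioner who knows the device, and a multiple-choice form does not rule out observer influence

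*Protocol article*

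**What the plan says.** All references are to the Protocol article.

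- **1 month.** The section headed "Questionnaire D2 – by the doctor – 1 month postoperative" lists: "Data collected are: complications, use of analgesics at that time, VDS pain score at rest, pain score while exercising and VDS cosmetic score".
- **12 months.** Form D3, also completed by the doctor, lists: "Collected data: recurrence, use of analgesics at that time, VDS pain score at rest, pain score while exercising and VDS cosmetic score".
- **Other time points.** The same pain and cosmetic items are on forms completed by the patient: P1 before surgery, P2 at 3 months and P3 at 24 months. The follow-up section confirms that the practitioner fills in D2 and D3 in clinic.
- **Blinding.** The patient is blinded and learns the device through P3. The analyst is blinded. Of the clinic visits the Blinding section says: "The consulted physician during follow-up is not blind for the received treatment".
- **The scale.** Data outcome defines the pain score through four words, none to severe: "The following terms are used in the VDS pain score, from which patients can choose to express the level of pain". It gives no matching definition for the cosmetic score.
- **The stated defence.** The Discussion says that the outpatient doctor could have been blinded, that this was left out for logistical reasons, and that "Observer-bias will be very little because of the straightforward multiple-choice questions in forms D2 and D3".
- **Role of the outcome.** Design gives the aim as to "determine the ideal treatment for patients with these conditions in terms of operation related complication and postoperative pain". The Abstract lists VDS pain and cosmetic scores as secondary endpoints.

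**The concern.** Pain and cosmetic appearance are subjective, and patient blinding is the trial's main protection for them. That protection works fully only if the blinded person's answer reaches the database unaltered. At 1 and 12 months it passes through someone who knows the device and who may have a view on which device is better. A blinded analyst cannot remove influence that is already in the recorded score.

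At stake is the credibility of the pain and cosmetic comparisons at those two visits. The Publication section plans reports at one month, one year and two years, so the first two coincide with the practitioner-completed visits. The Discussion tells the reader to expect very little observer bias, for a reason that does not carry that conclusion.

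**Working it through.** **1. Who records the score, and who is blinded**

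| Time | Form | Completed by | Does that person know the device? |
|---|---|---|---|
| Pre-operative | P1 | Patient | No (envelope opened later, in theatre) |
| 1 month | D2 | Practitioner | Yes |
| 3 months | P2 | Patient | No |
| 12 months | D3 | Practitioner | Yes |
| 24 months | P3 | Patient | Uncertain: P3 is also how the patient is told |

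The Post-operative section of the statistical method lists 1, 3, 12 and 24 months. Practitioner-recorded: 2 of 4, that is 50%. Patient-completed and securely blinded: possibly only 3 months, given the double role of P3.

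**2. What the text does and does not ensure**

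- For pain, the patient chooses the word. Read together with D2 and D3, the natural picture is that the patient answers and the practitioner writes. The route left for influence is how the question is put and how a hesitant answer is recorded.
- No instruction requires the patient to pick the word from a list unaided, or the practitioner to copy it unchanged.
- For the cosmetic score, nothing says whose judgement it is.
- Fixed categories limit the wording of an answer. They do not determine whether a hesitant patient is recorded as having no pain or mild pain.

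**3. Which analyses are affected**

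The stated tests compare the arms (Mann–Whitney, Pearson's chi-square or Fisher's exact). At each visit both arms have the same kind of recorder, so alternating between patient and practitioner does not by itself bias those comparisons. What matters is the practitioner's knowledge of the device at 1 and 12 months.

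**4. How a one-sided recording shift would act (illustration only)**

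The documents give neither a pain rate nor a recording error rate, so both are assumed.

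- Evaluable per arm: 346 × 0.90 / 2 = 155.7, taken as 156 (346 randomised and 10% loss, from the sample-size section).
- No true difference. A proportion *p* in each arm has any pain. In one arm only, a fraction *f* of those patients is recorded as having none.
- Recorded rates: *p* against *p*(1 − *f*).
- Probability of a significant result: sum, over all pairs of binomial counts, of the chance of each pair for which the two-sided 5% Pearson chi-square test rejects.

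| *p* | *f* | Recorded rates | Chance of p < 0.05 |
|---|---|---|---|
| 30% | 0 | 30% v 30% | 0.05 |
| 30% | 1 in 10 | 30% v 27% | 0.09 |
| 30% | 1 in 5 | 30% v 24% | 0.22 |
| 30% | 1 in 4 | 30% v 22.5% | 0.33 |
| 40% | 1 in 5 | 40% v 32% | 0.32 |

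Check of the third row by normal approximation: the mean rate is 0.27 and the null standard error is √(2 × 0.27 × 0.73 / 156) = 0.0503. The standard error under the recorded rates is √((0.30 × 0.70 + 0.24 × 0.76) / 156) = 0.0502. The power is Φ((0.06 − 1.96 × 0.0503) / 0.0502) = Φ(−0.77) ≈ 0.22.

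The table collapses the four levels to any pain, which the protocol does not define as an endpoint. It shows how bias would inflate false positives and says nothing about how much bias there is.

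**The case against.** The strongest reply is that the blinded patient chooses the pain word and the practitioner only writes it down, so the documents show a change of recorder and not of rater. This stands for pain, and it is why a reader should not infer that the doctor judges the patient's pain at 1 and 12 months. It does not extend to the cosmetic score, and it does not ensure faithful elicitation.

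Second, the lack of blinding is disclosed and argued. That also stands: this is neither a contradiction nor a hidden gap. Fixed answers chosen by a blinded patient do limit observer influence. The fault lies in concluding that little remains.

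Third, a reader might infer that the switch between patient and practitioner confuses the course of pain over time. The article states no change-from-baseline or longitudinal analysis, so that harm attaches to no planned result.

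Fourth, the figures of 22% to 33% might be read as the trial's false-positive rate. They rest wholly on an assumed misrecording in one arm and none in the other, for which the documents give no basis.

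Fifth, the patient-completed visits are not a perfect reference. Non-responders get a telephone questionnaire, whose taker's blinding is not stated, and P3 discloses the device. Resting the pain conclusion on those visits alone could leave only 3 months securely blinded.

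**Conclusion.** The concern holds in a limited form. Two of the four post-operative comparisons of VDS pain and cosmetic score, at 1 and 12 months, pass through a practitioner who knows the device. The possible influence lies in eliciting and recording the answer. Its size cannot be found from the documents, and the multiple-choice format does not rule it out. The exposure is clearer for the cosmetic score, which is not defined as the patient's choice.

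These are secondary endpoints, although postoperative pain is named in the trial's aim. The point does not affect the sample size. The same practitioner also records complications, the primary endpoint, on D2; that is a separate matter, which this change does not address.

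The change is worth making because it is cheap. It also avoids the logistical obstacle cited against a blinded doctor, since the person completing the items is already blinded and already attending.

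**What to change.** 1. Move VDS pain at rest, VDS pain on exercise and the VDS cosmetic score from D2 and D3 to a short sheet. The blinded patient completes it before the 1- and 12-month consultations, with the same items as on P2.
2. Leave analgesic use on the practitioner's form. The Definitions section counts prescribed painkillers other than paracetamol after discharge as a complication, so the item bears on the primary endpoint.
3. Replace the Discussion sentence with a plain limitation: scores recorded by an unblinded practitioner may be subject to observer influence of unknown size.
4. For visits already done, keep the data. Flag who recorded each score, telephone contacts included, and run a sensitivity analysis of the between-arm comparison by recorder. Read it descriptively, because the recorder will follow the enrolment period.
5. Make sure the 24-month scores are completed before the patient is told the device, for example by sending that information after P3 is returned.

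Cost: one form amendment and one sheet at two visits that already take place, with no extra staff or visits. Some sheets will come back blank. Because inclusion began in February 2011, the 1- and 12-month data will mix practitioner-recorded and patient-completed scores for patients already enrolled.
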